**10.2.1 Overview of Procedures and Immunologic Assays**

Immunizations 1, 2, 3 and 4 will be given at days 0,7,14 and 21, respectively. Mucosal biopsies and rectal secretions will be obtained at days –28 and –14 (baselines) and at days 10 and 24 and 6 and 12 months post day 0 (to assess durability of response). Mucosal biopsy specimens (up to 20 per donor /per procedure) will be obtained and processed within 15 minutes of harvest of the biopsies. We will also collect and test plasma for antibody days -42, -14, 10, 17, 24 and 6 and 12 months. Blood will be obtained at days -42, -28, -14, 0, 7, 10, 14, 17, 24, months 6 and 12 (and as needed per subject request for HIV status) to characterize the cellular immune responses and quantitative lg responses.

10.2.2 Measurement of HIV-1-specific antibodies in rectal and oral secretions

At both baseline and each post-immunization sigmoidoscopy visit we will measure HIV-1 antibodies from rectal secretions using the Weck-Cel method and from oral secretions using OraSure®. This involves collection of fluids into Weck-Cel sponges per a protocol developed by Kozlowski et.al. (JAIDS 24:297-309, 2000) or onto the OraSure® plegette according to the package insert. The pre-moistened sponges are inserted 5cm into the rectum of the subject via lubricated applicator pipette. The sponge is held in for 5 minutes and withdrawn. The procedure is repeated with a second sponge at the same location. The plegettes are inserted into the mouth, rubbed along the buccal mucosa few times and held there for 2 minutes. The absorbed antibodies are eluted by centrifugation in a two step process with elution buffer containing protease inhibitors into a pre-weighed collection tube. The collected fluids are diluted 1/10 in ELISA diluent and assayed for HIV–specific antibodies using the Vironostika® HIV-1 ELISA kit as per the manufacturer’s instructions with the inclusion of a standard curve generated from a purified anti-p-24 antibody (ImmunoDiagnostics, Inc). In addition, samples are assayed for total IgG, IgM and IGA content by ELISA. In brief, samples are incubated in wells pre-coated with anti-human IgG, IgM or IgA (DAKO Corp) washed and developed using horse-radish peroxidase conjugated secondary antibodies (Dako Corp) and OPD substrate. Purified human immunoglobulin standards (Jackson Labs) are included for each immunoglobulin and standard curves are generated. The total immunoglobulin content of the samples is calculated by the sum of the IgG, IgM and IgA. Results are expressed as units of HIV antibody per 100ug of total immunoglobulin. The collection and quantification assays for assessing secreted mucosal antibodies (rectal and oral) have been validated.

**10.2.3 Expansion of mucosal lymphocytes in vitro**

Using bi-specific antibodies provided by [name], isolated mucosal lymphocytes are expanded in a polyclonal manner through co-stimulation of CD3 and CD4 and CD3 and CD8. Using this protocol, 1 X 105 lymphocytes can be expanded into several million CD4+ or CD8+ lymphocytes. Because the expansion is driven by antibodies to surface antigens and not by viral antigens, this method expands T-cells in a polyclonal manner and therefore should not significantly alter relative frequencies of T-cell subpopulations. Expanded cells both PBMC and MMC will be used in chromium release assays, ELISPOT, and proliferative assays. For this assay, 105 gut lymphocytes, or 105 freshly ficolled PBMC are set up in a well of a 24-well plate containing: 105 lymphocytes to be expanded + 106 irradiated (3000 rad) autologous PBMC in 2ml of RPMI with 10%FCS and 50U/ml IL-2 (R10-50) containing 2g/ml of a bispecific CD3:CD4 antibody or the bispecific CD3:CD8 antibody.

**10.2.4 ELISPOT Analysis for IFN-for fresh PBMC, expanded PBMC and MMC**

Enzyme Linked-ImmunoSpot (ELISPOT) assay is performed as described by Tary-Lehmann et al. Briefly, 1 X 105 to 3 X 105 lymphocytes are plated in 96 well Unifilter plates (Whatman Inc. Cliffton, NJ) that have been incubated with INF- antibodies (4 g/ml) (Pharmingen, Carlsbad, CA) and blocked with PBS-BSA. For antigen stimulation: 100 l of canary pox virus (either ALVAC or ALVAC-HIV (vCP205) and HIV specific peptides are added to the plate at 5 pfu/cell. As a positive control, antibodies to CD2/2R and CD28 (Becton Dickinson Immunocytometry Systems, San Jose, CA) are added at 5 g/ml and 20 g/ml respectively. After 24 hours at 37oC, the plate is washed, and 100 l biotinylated IFN- (2g/ml) (Pharmingen, Carlsbad, CA) added and incubated for 24 hours at 4oC. After washing, 100 l diluted (1:2000) Streptavidin-HRP (Pharmingen, Carlsbad, CA) is added for 2 hours. The plate is washed again and the color developed by the addition of 200 l of visualization solution (24 ml of 0.1M acetate buffer with 800 l of AEC solution [10mg AEC/ml DMF] and 12 l of H2O2 [30%]) and subsequent incubation for 20 minutes at room temperature in the dark. Tap water is used to stop the reaction and the plate is air-dried. An ImmunoSpot Analyzer will be used for computerized analysis.

- - 1. **Chromium release assay for cytotoxicity**

Chromium release assays will be performed on the expanded CD8+ cell lines (See 10.2.3 above) as described in the preliminary results per standard protocol. Briefly, autologous EBV-transformed B-cell lines will be infected overnight with recombinant vaccinia virus for use as target cells. These cells will be labeled with 51Cr. In a 96-well U-bottom plate, 104 target cells will then be plated with effector-target cell ratios of 12.5:1, 25:1, 50:1 in duplicate for a 4 hour incubation, followed by determination of supernatant 51Cr on 96 well scintillation plates (LumaPlate, Packard; MicroBeta 1450, Wallac).

**10.2.6 CD4 T cell proliferation measured by ELISPOT Analysis for IL-2**

CD4 T cells will be assayed either immediately following isolation or after non-specific expansion as described above. Briefly 1 x 105 to 3 X 105 CD4 cells will be plated in 96 well Unifilter plates that have been coated with IL-2 antibodies and blocked with PBS-BSA. For antigen stimulation: 100ul of canary pox virus (either ALVAC or ALVAC-HIV (vCP205) at 5pfu/cell or HIV specific peptides at 100 ug/ml. As a positive control, antibodies to CD2/2R and CD28 are added at 5 and 20ug/ml respectively. After 24 hours at 37C the plate is washed and 100ul of biotinylated IL-2 (2ug/ml) is added and incubated for 24 hours at 4C. After washing, 100ul of diluted (1:2000) streptavidin-HRP is added for 2 hours. The plate is washed again and the color developed by the addition of 200 ul of visualization solution and subsequent incubation for 20 minutes at room temperature in the dark. Tap water is used to stop the reaction and the plate is air-dried. An ImmunoSpot Analyzer will be used for computerized analysis. The assays have been performed by the laboratory using PBMC with sensitive reproducible and specific results.

## 10.2.7 ELISA based assay for RANTES production

## To culture lymphocytes (PBMC or MMC) for the detection of *in vitro* RANTES production, 4 x 104 to 4 x 106 cells are cultured in IL-2 (1000 units/ml) in 24 well, flat bottom plates (Becton Dickinson, San Jose, CA). For non-specific stimulation, PWM 10 ug/ml), PHA 5 ug/ml), or antibodies to CD2/2R and CD28 (Becton Dickinson, San Jose, CA) are added at 10 g/ml and 20 g/ml respectively. Antigenic stimulation will be performed as described above for ELISPOT. 1 ml supernatants are harvested at 24 hr, day 10, and day 14 and 1 ml of fresh media added. For quantitation, samples are diluted 1:2 in RPMI with 10% FCS and plated with 100 l of assay diluent (RD1A) on the RANTES ELISA plate (R&D Systems, Minneapolis, MN). When needed, supernatants have been further diluted 4-, 6-, or 10-fold. 100 l of standard provided in the ELISA Kit (R&D Systems, Minneapolis, MN) is added to the plate as well and incubated at room temperature for 2 hours. The plates are washed, conjugate is added at 200 l per well and the plate is incubated at room temperature for 1 hour. Plates are washed and 200 ml of substrate solution is added and the plates are incubated for 20 minutes at room temperature. 50 ml of stop solution is added and the plate is read at 450 nm on an ELISA reader (Spectra Max 340 from Molecular Devices, Sunnyvale, CA).

**10.2.8 Quantitative image analysis (QIA) for *in vivo* RANTES production**

Cryopreserved colon biopsies, embedded in OTC-compound (Tissue-TEK, Mites, Elkhart, IN), will be cut in 8 µm thick sections and fixed with 2% formaldehyde. Slides will be incubated with polyclonal affinity-purified, biotinylated RANTES (R&D Systems, Minneapolis, MN), followed by an avidin-biotin horseradish peroxidase complex (Vectastain elite kit, Vector Laboratories, Burlingame, CA, USA) and counterstained with hematoxylin. Digital images of stained samples will then be transferred from a DMR-X microscope (Leica, Wetzlar, Germany), into a computerized image analysis system, Quantimet 550IW, (Leica, Cambridge, UK), which allows detection of 16.7 million different colors. For analysis, percentage positive area in the total of 2-8 fields, depending on the size of the biopsy, with a total mean area of 2.2 X 105 m2, will be assessed for positive-stained area and the total area of hematoxylin positive cells present. Semiquantitative results will be expressed as percentage positive area of total tissue area.

**10.2.9 Cytotoxic T lymphocyte epitope mapping**

We will non-specifically expand CD8+ cells from the gut and peripheral blood. As also shown in the Preliminary Results, a further round of antigen specific stimulation will be performed, using recombinant vaccinia virus-infected autologous EBV-transformed B-cells, as per the method of Lubaki et al. This will be followed by limiting dilution cloning and fine mapping as per published methods. We have already successfully isolated HIV-1-reactive clones from the peripheral blood of an infected individual using these methods.

**10.2.10 Flow cytometric analysis for 47 expression on PBMC and activation markers (HLA-DR and CD-38) on PBMC and MMC**

Expression of 47 is required for successful homing of peripheral lymphocytes to the gastrointestinal compartment. As an indicator of the percentage of blood lymphocytes which can potentially home to GALT in response to vaccination, immunofluorescent staining will be performed on PBMC isolated from whole blood by Ficoll-Hypaque. One million PBMC will be co-stained with antibodies against CD3, CD4, CD8 (Becton Dickinson, San Jose, CA) and 47 (Integrin 7: BD Pharmingen, San Diego CA). Cells will also be stained in parallel with isotype controls. Samples will be assessed on a FACSCalibur flow cytometer. Similar protocols will be performed assessing changes in HLA-DR and CD-38 (Becton Dickinson, San Jose, CA) expression on CD4 and CD8 T lymphocyte subsets in both freshly acquired PMBC and MMC.

- 1. **HIV-1 Virology**
     1. **Detection of intercurrent HIV-1 infection by HIV-1 PCR**

The ALVAC-HIV (vCP205) vaccine includes *gag* and *pol* gene products as well as *env* (gpl60), in its composition. Consequently, the confirmatory Western Blot serologic assay may be unable to distinguish a vaccine-induced immune response from natural infection in study subjects. Overall, several precautionary measures will be taken to clarify this distinction between vaccine-induced antibody responses and those from intercurrent HIV-1 infection:

1. Only volunteers at lower risk for HIV-1-infection will be considered for enrollment. Volunteers will be counseled frequently during the trial on avoidance of HIV-1 infection.

2. Subjects will have frequent clinical evaluations for signs or symptoms of an acute HIV-1 infection syndrome. An intercurrent illness consistent with HIV-1 infection or circumstances suggesting increased risk of acquiring HIV-1 (e.g., report of higher risk behavior, newly acquired STD, report of unsafe sexual activity with an HIV-1-infected individual) would prompt a diagnostic work up.

1. Periodic HIV-1 ELISAs and Western Blots will be performed. If intercurrent HIV-1 infection is suspected, further diagnostic work-up will be performed.

All subjects who have positive HIV-1 serology at the end of the study as measured by an FDA-approved HIV-1, 2 ELISA and/or Western Blot kit, will be offered follow-up HIV-1 diagnostic testing by HIV-1 RNA PCR through the [name] Lab after the completion of the study. In addition, the participants will be given money to cover the approximate clinical cost of three PCR tests when the participant or his/her healthcare provider feels it is indicated.

- 1. **Calendar of Studies**

The subjects will have 3 baseline visits with blood draws and two sigmoidoscopies to establish baseline measurements of immune function and screen for any exclusion criteria. They will then begin an intensive series of vaccinations and measurements for safety and immunologic response. Subjects will have a total of 880 ml of blood drawn over the 14 months of the study. No more than 450 ml will be drawn in any 8 week period. The subjects will be encouraged to report any unusual symptoms that may be related to the study and may make a visit with clinical staff at any point between any of the following study visits. The scheduled intervals between visits may vary by several days due to scheduling or other difficulties.

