## Day - 42(Screening)

- Signed enrollment consent form
- Completion of Participant Profile form, including medical history
- Counseling on avoidance of HIV-1 infection and pregnancy – handout signed
- Complete clinical evaluation (temperature, vital signs, and physical exam)
- Complete STD examination
- Blood draw as follows
- 10 ml untreated “SST” - chem panel & HCG
- 35 ml untreated “Red Top” for Hepatitis B and C antibody screening (10ml), HIV-1 antibody ELISA (10ml) canarypox antibody – research (10 ml) RPR (5ml)
- 20 ml EDTA “Lavender Top” - for CBC (5ml), CD4/8 & HLA phenotyping (5ml), HIV-1 RNA PCR (10ml)
- 60 ml heparinized “Green Top” – for cryopreservation of feeder cells

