# Day -28 (Baseline immune responses; mucosal biopsies #1)

- Counseling on avoidance of HIV-1 infection and pregnancy – handout signed
- Blood draw as follows:
- 10 ml EDTA “Lavender Top” for HIV-1 antibody - research
- 90 ml heparinized “Green Top” for CTL assays
- Weck-Cel and OraSure secretion collection
- Sigmoidoscopy (up to 20 specimens collected for baseline screening for CTL activity)
- Give participant post-procedure home care instructions

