## Day 24 (3 days post-immunization #4; safety and immune responses; mucosal biopsy #4)

## AE assessment

- Risk reduction counseling on avoidance of HIV-1 infection and pregnancy
- Examination of sites of immunization
- Note changes in injection site and surrounding area
- Blood draw as follows:
- 5 ml untreated “SST” for chem panel
- 20 ml untreated “Red Top” for HIV-1 antibody ELISA (10ml) canarypox antibody – research (10ml)
- 25 ml EDTA “Lavender Top” for CBC (5ml), CD4/8 count (5ml) HIV RNA PCR (5ml) HIV antibody - research (10ml)
- 60 ml heparinized “Green Top” for CTL assays
- Weck-Cel and OraSure secretion collection
- Sigmoidoscopy (up to 20 specimens collected)
- Give participant post-procedure home care instructions

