###### As needed

###### Risk reduction counseling on avoidance of HIV-1 infection

- Blood draw as follows:
- 10 ml EDTA “Lavender Top” for HIV-1 RNA PCR
  1. **Summary of Studies**

| DAY | -42 | -28 | -14 | 0 | 3 | 7 | 10 | 14 | 17 | 21 | 24 | Mo. 6 | Mo. 12 |  |
| --- | --- | --- | --- | --- | --- | --- | --- | --- | --- | --- | --- | --- | --- | --- |
| VISIT | 1 | 2 | 3 | 4 | 5 | 6 | 7 | 8 | 9 | 10 | 11 | 12 | 13 | PRN |
| Immunization |  |  |  | X |  | X |  | X |  | X |  |  |  |  |
| Sigmoidoscopy, Weck & OraSure |  | X | X |  |  |  | X |  |  |  | X | X | X |  |
| AE assessment |  | X | X | X | X | X | X | X | X | X | X | X | X |  |
| Risk Reduction Counseling |  | X | X | X | X | X | X | X | X | X | X | X | X | X |
| STD Examination | X |  |  |  |  |  |  |  |  |  |  |  |  |  |
| Injection Site Evaluation |  |  |  |  | X | X | X | X | X | X | X |  |  |  |
| **PBMC’s** |  |  |  |  |  |  |  |  |  |  |  |  |  |  |
| CBC, differential, platelets | X |  |  |  |  | X |  | X |  |  | X | X | X |  |
| T-Cell count | X |  |  |  |  | X |  | X |  |  | X | X | X |  |
| CD38* | X |  |  |  |  | X |  | X |  |  | X | X | X |  |
| 47* | X |  |  |  |  | X |  | X |  |  | X | X | X |  |
| B-cell line established** | X |  |  |  |  |  |  |  |  |  |  |  |  |  |
| HLA typing** | X |  |  |  |  |  |  |  |  |  |  |  |  |  |
| 51CR |  | X |  | X |  |  | X |  | X |  | X | X | X |  |
| ELISPOT*** |  | X |  | X |  |  | X |  | X |  | X | X | X |  |
| Cryo PBMC feeder | X |  |  |  |  |  |  |  |  |  |  |  |  |  |
| **Plasma** |  |  |  |  |  |  |  |  |  |  |  |  |  |  |
| HIV-1 RNA PCR | X |  | X |  |  | X |  | X |  |  | X | X | X | X |
| HIV Ab Research IgG, IgA |  | X | X |  |  |  | X |  | X |  | X | X | X |  |
| **Serum** |  |  |  |  |  |  |  |  |  |  |  |  |  |  |
| Chem panel | X |  |  |  |  | X |  | X |  |  | X | X | X |  |
| Pregnancy test (HCG) | X |  |  |  |  |  |  |  |  |  |  |  |  |  |
| HIV-1 antibody ELISA | X |  | X |  |  |  | X |  | X |  | X | X | X |  |
| HIV Ab Res - canarypox | X |  |  |  |  |  |  |  |  |  | X | X |  |  |
| RPR | X |  |  |  |  |  |  |  |  |  |  |  |  |  |
| HBV/HCV Ab | X |  |  |  |  |  |  |  |  |  |  |  |  |  |
| **Urine** |  |  |  |  |  |  |  |  |  |  |  |  |  |  |
| Pregnancy test |  |  |  | X |  | X |  | X |  | X |  |  |  |  |
| **Tissue** |  |  |  |  |  |  |  |  |  |  |  |  |  |  |
| QIA on frozen spec |  | X | X |  |  |  | X |  |  |  | X | X | X |  |
| **MMC’s** |  |  |  |  |  |  |  |  |  |  |  |  |  |  |

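### The listed blood draws from Day -28 to Day 24 add up to 465 ml in 52 days, above the protocol's own 450 ml limit for any 8 weeks

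*Protocol*

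**What the plan says.** The opening paragraph of Protocol section 10.4 (Calendar of Studies) makes three statements that matter here:

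- Total volume: "Subjects will have a total of 880 ml of blood drawn over the 14 months of the study".
- Rolling limit: "No more than 450 ml will be drawn in any 8 week period".
- Visit timing: "The scheduled intervals between visits may vary by several days due to scheduling or other difficulties".

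The visit entries that follow give a volume for every tube. The largest items are the heparinized tubes: at Day -28, "90 ml heparinized “Green Top” for CTL assays", and at Day 24, "60 ml heparinized “Green Top” for CTL assays". Section 10.2.1 names the same draw days and adds that blood may be taken at "months 6 and 12 (and as needed per subject request for HIV status". The as-needed entry in section 10.4 puts such a draw at "10 ml EDTA “Lavender Top” for HIV-1 RNA PCR".

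**The concern.** The 450 ml limit carries no qualifier. The word any makes it a rolling limit, so it must hold for every 8-week span, including the one that combines the baseline biopsy visits with the vaccination phase. That phase packs six blood draws into 24 days, close behind the 100 ml taken at Day -28. If the listed tubes exceed 450 ml on the planned days, site staff cannot follow both the calendar and the limit.

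What is at stake is a commitment about blood taken from healthy volunteers who, by the protocol's own account, are not expected to benefit directly. It is not a matter of inference.

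**Working it through.** **Inputs.** Tube volumes come from the visit entries in Protocol section 10.4. Days 3 and 21 list no blood draw.

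| Visit | Tubes (ml) | Total (ml) |
| --- | --- | --- |
| Day -42 | 10 + 35 + 20 + 60 | 125 |
| Day -28 | 10 + 90 | 100 |
| Day -14 | 10 + 15 | 25 |
| Day 0 | 30 | 30 |
| Day 7 | 5 + 15 | 20 |
| Day 10 | 10 + 10 + 60 | 80 |
| Day 14 | 5 + 15 | 20 |
| Day 17 | 10 + 10 + 60 | 80 |
| Day 24 | 5 + 20 + 25 + 60 | 110 |
| Month 6 | 5 + 20 + 25 + 90 | 140 |
| Month 12 | 5 + 10 + 25 + 90 | 130 |

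Where an entry splits a tube type into sub-volumes, the parts add up to the stated amount, so the totals do not depend on how a line is read.

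**Step 1: the stated study total.** The scheduled draws sum to 125 + 465 + 140 + 130 = 860 ml, where 465 ml is the Day -28 to Day 24 subtotal from Step 2. The protocol states 880 ml. The difference is 20 ml (20/880 = 2.3%), and the text does not explain it. The two figures are close enough to suggest that the calendar has been read as intended.

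**Step 2: the rolling 8-week totals.** Eight weeks is 56 days. For each starting visit, sum every draw within the next 56 days on the nominal calendar.

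- From Day -42: 125 + 100 + 25 + 30 + 20 + 80 = 380 ml. Day 14 is exactly 56 days later; counting it gives 400 ml.
- From Day -28: 100 + 25 + 30 + 20 + 80 + 20 + 80 + 110 = 465 ml. Day 24 is 28 + 24 = 52 days later, so it is inside the window under any counting rule.
- From Day -14: 25 + 30 + 20 + 80 + 20 + 80 + 110 = 365 ml.
- Windows that start later are smaller.

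**Step 3: comparison with the limit.** 465 - 450 = 15 ml, and 15/450 = 3.3%. Only the window from Day -28 exceeds the limit.

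**Step 4: sensitivity.**

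- Section 10.2.1 leaves Day -28 out of its list of plasma antibody days, whereas the calendar and the Summary of Studies table include it. Dropping that 10 ml tube still gives 455 ml.
- One as-needed draw of 10 ml inside the window would give 475 ml.
- If the Day -28 to Day 24 interval stretched from 52 to 57 days, the two visits would no longer share a window. The sum would split into 355 ml (Day -28 to Day 17) and 365 ml (Day -14 to Day 24).
- Slippage can also go the other way. Day -42 and Day 17 are 59 days apart. Shortened to 55 days or fewer, that span would hold 125 + 100 + 25 + 30 + 20 + 80 + 20 + 80 = 480 ml.

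**The case against.** The strongest reply is that the limit is the controlling rule and the calendar bends to it. The same paragraph allows intervals to vary, and staff who watched the running total could space the visits out or trim a tube. This softens the contradiction without removing it. The timing sentence is a tolerance for scheduling difficulties, not an instruction to protect the limit. A subject who attends every visit on the planned day goes over.

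Three further objections have some force:

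- **Size.** An excess of 15 ml spread over eight draws in screened healthy adults is small. That is accepted, and it keeps the point minor.
- **As-needed draws.** The protocol summary ties subject-initiated visits and PCR testing to the extra year of follow-up, and HIV RNA PCR is already scheduled at Days -14, 7, 14 and 24. A requested draw inside this window is therefore possible but unlikely. The 475 ml figure shows what the text permits, and the conclusion does not rest on it.
- **The 880 ml total.** It overstates the scheduled blood by 20 ml and breaks no limit. The gap equals two 10 ml as-needed draws, although the protocol does not give that as the reason. It calls for tidying up and is not evidence of the breach.

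**Conclusion.** The concern holds. On the nominal calendar, the draws from Day -28 to Day 24 total 465 ml in 52 days, against an unqualified limit of 450 ml in any 8 weeks. The excess is 15 ml (3.3%), in that one window.

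The result assumes only that the listed tubes are filled as stated and that visits occur on the listed days. Spacing that takes the Day -28 to Day 24 interval beyond 56 days would avoid the excess for a given subject, but the protocol does not require it.

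Severity is minor: the schedule misses a stated limit on blood volume, and no effect on endpoints, sample size or analysis is shown.

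**What to change.** Either of two changes resolves it.

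1. **Restate the limit.** Set it to at least 465 ml plus an allowance for as-needed draws, for example 465 + 2 × 10 = 485 ml, with IRB approval. This changes one sentence and leaves the schedule alone, so it is the simpler option.

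2. **Move the first biopsy visit earlier.** It has to fall more than 8 weeks before Day 24, with screening kept more than 8 weeks before Day 17. Day -33 is 57 days before Day 24 and leaves no slack. Day -35 is 59 days before and leaves 2 days. In both cases the largest nominal window is 400 ml, which leaves 50 ml, or five as-needed draws. The visit moves by 5 to 7 days, with two side effects. At Day -35, screening precedes the first sigmoidoscopy by 7 days instead of 14, and the two baseline biopsies are 21 days apart instead of 14. Because visits may vary by several days, the minimum interval should be written as a requirement.

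Cutting the Day -28 heparinized draw from 90 to 60 ml would bring the largest window to 435 ml. This is an option only if the laboratory confirms that 60 ml is enough. Months 6 and 12 use 90 ml for the same PBMC assays marked in the Summary of Studies table, and the protocol does not give cell yields or needs per assay, so the cost cannot be judged from it.

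Whichever route is chosen, reconcile the stated 880 ml with the 860 ml scheduled, for instance by saying whether the total includes as-needed draws.
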